## Method

### Intervention

#### The online platform

KopOpOuders-PTSD consists of five weekly online modules and three face-to-face sessions with a professional (see Additional file 2 for a summary of the modules and sessions). The online modules can be accessed through an online platform. Each module follows the same structure, with components such as reflection on the past week, videos of interviews with other parents with mental illness, and a homework exercise. Modules take ca. 30–45 minutes each to complete, and homework exercises ca. 20 minutes. In addition to the online modules, the platform also contains a ‘library’ with additional information about PTSD and other mental illnesses, how to explain these to children, their potential impact on children, and risk and protective factors. Finally, the platform contains a ‘self-care hub’ with content such as relaxation exercises and positive writing exercises [38].

#### Adapting KopOpOuders self-help into KopOpOuders-PTSD

KopOpOuders Self-Help was adapted for the PTSD population in three ways: integration of perspectives and needs of parents with PTSD; expansion from online to blended care; and addition of PTSD-specific content.

#### Integrating parents’ PTSD-specific needs

To ensure that the form and content of KopOpOuders-PTSD matches the wishes and needs of the target group, we adopted a co-creation approach, in which we collaborate with an advisory board of parents with PTSD and their partners. The advisory board fluctuated in size and composition throughout the development of the intervention, ranging from three to six members. Input from advisory board members was obtained in focus group-like meetings from the start of intervention development and will continue to the end of the study. As far as possible within the small group, we strived to ensure diversity in gender, ethnic backgrounds, (dis) abilities and family compositions. Whereas the current advisory board is diverse in most aspects, some groups (e.g., single-parent families, LGBTQIA+ families, families with infant children) were not sufficiently represented. Apart from diversity, we also strive for inclusivity in the advisory board. This means that we endeavor to make all members feel equally valued, respected, and safe to be themselves; that we compensate members for their expertise; and that we continue to acknowledge and challenge our own privilege and biases.

The knowledge gained from the advisory board was supplemented with results from a mixed methods study we conducted among parents with PTSD. In this study, parents were asked about their wishes and needs for parenting support and their opinions on aspects of the intervention protocol. Table 1 presents an overview of adaptations to the study protocol and intervention design based on input from the advisory board and mixed methods study.

**Table 1 Tab1:** Intervention and study design decisions based on input from advisory board and mixed methods study

**Source**	**Intervention: Online Modules**
Advisory board	Advisory board members pointed out module content was sometimes too confrontational, which could be improved through small changes. E.g., green and red markers to denote parenting strengths and difficulties, were replaced by neutral-colored markers labeled ‘this is something I do well’ and ‘this is something I find challenging and want to learn more about’.
Advisory board, Mixed methods study	To every online module, extra texts were added which provided a PTSD-specific perspective on the module topic. The content of these texts was based on the personal experiences of advisory board members and mixed methods study participants.
Advisory board	Advisory board members suggested adding more concrete ‘tips and tricks’ to the extra texts. We based these partially on tips that the board members and their families use themselves.
Advisory board	Advisory board members emphasized the importance of leaving the house, exercising, and social connection for relaxation. We therefore added more tips about this, balancing out the tips which had been more focused on being alone and at home (e.g., yoga and meditation).
	**Intervention: In-Person Sessions**
Advisory board, Mixed methods study	Opinions were mixed on whether to carry out sessions one-on-one or in a group with multiple parents. Most parents expressed concerns about privacy and trust in group settings, while also seeing value in the recognition that could be gained from hearing other parents’ experiences. In the end, we decided on one-on-one sessions. The element of recognition was promoted by presenting the extra texts in the online modules as conversations between fictionalized parents with PTSD sharing their struggles and advice with each other.
Advisory board	Advisory board members recommended “do’s and don’ts” for the professionals leading the sessions (e.g., being aware of potential mistrust in institutions, especially in veteran parents; parents appreciate it when professionals are well-prepared, having an open and accepting attitude, and refraining from assumptions and judgment). These were integrated in the protocol and training for professionals.
Advisory board, Mixed methods study	The following themes, which advisory board members and mixed methods study participants raised as important, were integrated in the protocol for the in-person sessions: - On the one hand, parents experience shame and guilt towards their children/family for having PTSD; on the other hand, they also experience shame and guilt about recovering from PTSD, perceiving themselves as “too self-absorbed” or “not available enough” (e.g., being too tired after therapy sessions to participate in family activities). Recognizing and reducing these conflicting feelings is important; - Practical tips for communication with family when feeling overwhelmed or being triggered; - Recognizing and reducing overprotectiveness and overcontrol in the home and family setting.
Advisory board	All advisory board members emphasized the importance of involving the partner. We therefore adapted the protocol of the final session, so that parents can bring their partner (or other significant person) to discuss their progress and how the partner can support them.
	**Ecological Momentary Assessment**
Advisory board	The assessment schedule was changed, to make it less demanding and more flexible, due to concerns from the advisory board about the difficulty of completing EMA assessments during busy times with their child.
Advisory board	Items about sleep quality and overall distress level were added, because advisory board members pointed out these aspects had a large impact on how their day was going to be.
	**Recruitment Materials**
Advisory board	The recruitment flyer was changed to be simpler and less text-heavy; advisory board members remarked that the setting in which the flyer would be encountered (the treatment center) is an environment in which they often feel tense and would have insufficient focus to read large amounts of text.

#### Expansion to blended care

The three minimal contact moments were replaced by three 90-minute in-person sessions with a preventive mental health professional. To uphold the emphasis on parental autonomy and self-direction while instituting more extensive contact with a professional, the role of the professional is that of ‘facilitator’ rather than ‘leader’. All professionals receive a 12-hour training, and sessions are carried out according to a manual to ensure consistency. Whereas the content of the online modules remains largely the same as in the original KopOpOuders Self-Help-intervention (and thus applicable to a wide range of mental health and addiction problems), the in-person sessions have a more in-depth and PTSD-specific focus. In the sessions, parents receive psychoeducation about PTSD and parenting, are encouraged to ask for individualized guidance, and get the opportunity to practice newly learned skills. In-person sessions are carried out one-on-one, but parents are encouraged to bring a partner or other significant person in the final session.

#### Addition of PTSD-specific content

In KopOpOuders-PTSD, the transdiagnostic (i.e., not specific to any one diagnosis) protective factors of KopOpOuders Self-Help are supplemented with PTSD-specific factors. This is done in two ways. Firstly, intervention themes are approached from a PTSD-specific perspective in in-person sessions. For example, one of the themes in KopOpOuders Self-Help is ‘talking to your child about your illness’. After parents learn about this in a more general way in the online module, the following in-person session addresses PTSD-specific aspects, including constructive and age-appropriate ways to talk to children about PTSD and trauma. Secondly, PTSD-specific content is added to the online intervention, which parents can refer to according to their own needs. The content is presented in the form of written conversations between fictional parents with PTSD, to increase relatability and recognition. The written conversations cover topics such as recognizing and dealing with triggers in the family setting, and the impact of PTSD-related avoidance and dissociation on children.

### Setting

Inclusion of participants started June 1st, 2022, and is expected to finish December 31st, 2023. Participants are outpatient clients in treatment for PTSD at Arkin Mental Health Care, a Dutch mental health care provider based mainly in the city Amsterdam. Clients from several Arkin Mental Health Care departments can participate: Sinai Centrum (for clients with primary diagnosis of PTSD), Jellinek (for clients with primary diagnosis of substance use disorders), Arkin BasisGGZ (for clients receiving low-intensity basic mental health care) or NPI (for clients with main diagnosis of personality disorders). PTSD treatment at these centers, which we refer to as Treatment as Usual (TAU), consists of Eye Movement Desensitization and Reprocessing, Imaginary Exposure, and/or Imagery Rescripting Therapy.

### Study design

This study uses a two-arm randomized controlled trial (RCT) design: the intervention condition receives KopOpOuders-PTSD in addition to TAU and is compared to a control condition which only receives TAU. This design allows us to test whether the effect of KopOpOuders-PTSD in addition to TAU is superior to that of TAU only. The randomization ratio is 1:1. Block randomization (2:4:6) is used, stratified by the Arkin Mental Health Care department (Sinai Centrum or other; clients of Sinai Centrum have PTSD as their primary diagnosis, whereas clients of other departments typically do not) to ensure even distribution across conditions. Double-blind randomization is not possible, because participants and prevention professionals providing in-person sessions know automatically whether the participant is receiving the intervention. Therefore, we apply single blinding, in which the researcher overseeing the assessments and analyzing the results is blind to the condition. Randomization is done by a research assistant who is not involved in the assessments. Randomization outcomes are only accessible to this research assistant. Participants are instructed not to share their randomization outcome with the researcher overseeing their assessments, and professionals carrying out the intervention are instructed not to discuss any identifying details of intervention participants with the researcher. Unblinding is possible if needed in case of (serious) adverse events, and can be done by the primary investigator, who is not involved in assessments. To ensure parenting support is not withheld due to participation in this study, control condition participants are invited to complete the online KopOpOuders-PTSD modules after their participation and will receive information about the parenting support options at Arkin Mental Health Care.

#### Measurement levels

In this study, we distinguish between ‘macro-level’ and ‘micro-level’ outcomes. With macro-level, we refer to longer-term retrospective reports on behaviors, attitudes, symptoms, etc. By contrast, we use the term micro-level to refer to moment-to-moment dynamics of behavior and interactions in daily life. Whereas the macro-level assessments in this study are useful to detect overall changes in parenting and mental health outcomes from pretest to posttest, they may not be able to fully capture the dynamic nature of parenting in daily life. This is especially relevant in PTSD, where symptoms can fluctuate strongly throughout the day, and PTSD-related memory impairments may bias retrospective assessments [77]. We therefore supplement macro-level assessments with micro-level assessments using ecological momentary assessment (EMA), a research method in which participants systematically and repeatedly report on current or recent behavior, emotions and/or thoughts [78]. EMA can provide rich, ecologically valid information on moment-to-moment parenting dynamics [77–79].

#### Macro-level assessments

All outcomes in this study are measured at the macro-level using questionnaires at three measurement points: pretest (week 0), posttest (week 10), and follow-up (week 22). All questionnaires are completed by participants using the online platform Castor Electronic Data Capture [80].

#### Micro-level assessments

Micro-level assessment of parenting and PTSD symptoms is carried out through EMA at pretest and posttest. Participation in the EMA component of the study is optional. Participants who choose to take part can do so by installing the app ‘Ethica Data’ [81] on their smartphone. The Ethica Data-app sends a brief EMA-questionnaire at three moments per day: at the end of the morning (randomly between 11:00–12:00), afternoon (randomly between 16:00–17:00, and evening (randomly between 21:00–22:00). If a questionnaire is missed, a reminder signal is sent after 60 minutes. Questionnaires are locked after 120 minutes to preserve the ‘real-time’ effect and prevent accumulation of questionnaires.

### Participants

#### Sample size

We assumed a medium effect size for the primary macro-level outcome (parenting behavior: Alabama Parenting Questionnaire), *d* = 0.55, based on RCTs with similar designs, interventions and populations as the current study, and with the same primary outcome [21, 82]. With a power of 0.80 and significance level of *p* = .05, the minimum *n* is 53 per condition. From previous experience with intervention studies in adults with PTSD, we expect 20–25% dropout. We therefore corrected with 25% oversampling, resulting in 53/0.75 = *n* = 71 per condition, total *N* = 142.

For the primary micro-level outcome (parenting behavior: Short Parenting Scale for EMA), power was calculated using PowerAnalysisIL [83] using our best estimation of relevant parameters. Based on existing EMA literature [84], we assume participants will respond to 70% of the 42 EMA prompts, resulting in 29 complete data points per participant. Assuming an autocorrelation between measurement occasions of *r =* 0.30 and a medium effect size, minimum sufficient power to detect intervention effects would be reached if *n =* 32 (16 per condition) agreed to take part in the EMA component of the study.

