##### Micro-level: real-time parenting behavior

When participants report being currently or recently in contact with the index child in the EMA questionnaire, parenting behavior is assessed using eight adapted items from the Parenting Behavior Inventory (PBI [91]). The Dutch translation of the PBI was obtained from Visser and colleagues [92]. The PBI contains 20 items which comprise two independent subscales: hostile/coercive and supportive/engaged. Items describe parenting behaviors, which parents rate for frequency on a seven-point Likert scale ranging from ‘Never’ (1) to ‘Always’ (7). The PBI has good psychometric properties, with excellent internal consistency for both independent subscales, adequate to good content validity, and good test-retest reliability [91]. We have selected eight PBI items, of which four from each subscale. The wording of these items has been changed slightly to fit with the EMA format (e.g., ‘I say mean things to my child that could make them feel bad’ becomes ‘This morning… I have said mean things to my child that could make them feel bad’). We have also changed the response scale to a three-point Likert scale: ‘Not true’ (1), ‘Somewhat true’ (2), ‘Certainly true’ (3). Scores on each of the two subscales range from 4 to 12. The total score of the two subscales combined ranges from 8 to 24. This total score will be used to test intervention effects (research question 2). For this study, we will call this questionnaire the ‘Short Parenting Scale for EMA’ (SPS-EMA). Because this novel adaptation of the PBI has not previously been used in EMA, we tested the SPS-EMA in a small-scale pilot study. We found the items to have sufficient frequency and variability for use with EMA.

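### The stated EMA minimum of 32 parents (16 per condition) is too low: it counts every answered prompt as a parenting score and leaves out the dropout the protocol expects

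*Protocol article*

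**What the plan says.** The Sample size section gives two calculations. For the questionnaire outcome it states "With a power of 0.80 and significance level of *p* = .05, the minimum *n* is 53 per condition". It then says "From previous experience with intervention studies in adults with PTSD, we expect 20–25% dropout", and divides by 0.75 to reach 71 per condition and 142 in total.

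For the EMA outcome it says "we assume participants will respond to 70% of the 42 EMA prompts, resulting in 29 complete data points per participant". It continues "Assuming an autocorrelation between measurement occasions of *r =* 0.30 and a medium effect size", and concludes that power suffices once "32 (16 per condition) agreed to take part in the EMA component of the study". No numeric power, effect-size metric, variance components or dropout allowance accompany this figure.

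The instrument section, Micro-level: real-time parenting behavior, sets a condition on the outcome: "When participants report being currently or recently in contact with the index child in the EMA questionnaire, parenting behavior is assessed using eight adapted items".

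Under Analysis, Micro-level: primary endpoint, the test compares conditions at posttest with control for pretest scores, using random intercepts. The second EMA week starts the day after the week-10 posttest. EMA is optional, and no upper limit on EMA participants is stated.

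**The concern.** Two inputs to the EMA calculation do not match the rest of the protocol.

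- **Data points.** The calculation is for the SPS-EMA, but the 29 counts answered questionnaires. An answered questionnaire that reports no current or recent contact with the index child yields no SPS-EMA score.
- **Dropout.** The 16 per condition is a number of parents who agree to take part at the start. A parent lost before week 10 supplies no posttest EMA. The loss that raises the questionnaire sample from 53 to 71 is not applied one paragraph later.

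Both omissions act in the same direction. Because EMA is optional, 32 is the protocol's only benchmark for whether research question 2, a primary question, has enough participants. If uptake ended near 32, the article would support calling that test adequately powered when its own dropout assumption says otherwise.

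**Working it through.** **Inputs from the protocol.** 42 prompts (21 per EMA week); 70% response; autocorrelation 0.30; a medium effect with no number; 16 per condition; dropout 20–25%; two-sided alpha .05; 1:1 allocation.

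**1. The protocol's own figures.**
- 42 x 0.70 = 29.4, stated as 29. The arithmetic is correct.
- A two-sample t-test with d = 0.55, power 0.80 and alpha .05 gives 52.9, so 53 per condition; 53/0.75 = 70.7, so 71. Both reproduce.
- The 16 per condition cannot be reproduced from the document, because power, effect metric and variance components are not given.

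**2. Dropout alone.** This step needs no model. If 16 per condition are needed with posttest data:
- at 25% dropout, 16/0.75 = 21.3, so 22 per condition (44 in total);
- at 20% dropout, 16/0.80 = 20 per condition (40 in total).

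The protocol used 25% for the questionnaires, so 22 is the consistent figure. Conversely, if only 16 per condition agree, 16 x 0.75 = 12 remain at posttest.

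**3. Contact gating alone.** Expected SPS-EMA scores per parent = 42 x 0.70 x c, where c is the share of answered prompts that report contact. The protocol gives no c. Assumed values:
- c = 1.0: 29.4 scores
- c = 0.8: 23.5 scores
- c = 0.6: 17.6 scores
- c = 0.4: 11.8 scores

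**4. What this could mean for power (illustration only).** One set of assumptions happens to return 16 per condition at power 0.80: the test is on change between the two weeks, the effect is 0.5 within-person SD, and there is a random intercept only. The variance of a weekly mean of m scores is inflated by (1 + 0.30)/(1 − 0.30) = 1.857.

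SE = sqrt[(2/n) x 2 x 1.857/m], and power = Φ(0.5/SE − 1.96). At full contact m = 14.7 per week.
- n = 16, c = 1.0: SE = 0.178, 0.5/SE = 2.81, power 0.80
- n = 12, c = 1.0 (25% dropout): SE = 0.205, power 0.68
- n = 12, c = 0.8 (m = 11.8): SE = 0.229, power 0.59
- n = 12, c = 0.6 (m = 8.8): SE = 0.265, power 0.47

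**5. Sensitivity to the unstated assumptions.** Modelling the autocorrelation exactly over the prompt sequence, with prompts missing at random, gives 0.87 for n = 16 at full contact. With 12 remaining it gives 0.77 at full contact, 0.70 at c = 0.8 and 0.61 at c = 0.6.

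Taking the effect as 0.5 total SD and adjusting posttest means for pretest means (ANCOVA), with an assumed intraclass correlation of 0.2 to 0.5, gives:
- full contact: 0.93–0.98 with 16 per condition, 0.85–0.94 with 12
- c = 0.6: 0.79–0.90 with 16 per condition, 0.67–0.80 with 12

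The direction is the same in every variant. The size is not.

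**The case against.** The strongest reply is that nothing here shows the EMA test to be underpowered, and that reply is right.

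- **Power not delivered.** A reader might infer that a promised power is not achieved. The protocol states no numeric EMA power; 0.80 is borrowed from the questionnaire calculation. Under the total-SD ANCOVA assumptions, 12 parents per condition with full contact still exceed 0.80.
- **The trial will fall short.** The 32 is a floor on an optional component open to all 142 participants, not a recruitment target or cap. Even 44 parents would be only 31% uptake (44/142).
- **A specific corrected minimum.** Any figure beyond 22 per condition requires a contact rate and an effect metric that the document does not give. It might also be inferred that 16 per condition works only if parents do not differ in how much they change. That is true of the reconstruction in step 4, but it is not shown for the sponsor's calculation.
- **Contact may be frequent.** The items cover recent as well as current contact, and the sample item asks about the morning as a whole. Prompts come at the end of each part of the day, and parents with no contact with their children are excluded. Heavy loss of prompts to school or work should therefore not be presumed. Nor can the contact rate be assumed known from the SPS-EMA pilot: the article reports only that the items were frequent and variable enough.

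The planned multiple imputation does not answer the dropout point. It applies equally to the questionnaires, for which the protocol still enlarged the sample.

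What remains is that the minimum rests on two inputs that the rest of the protocol contradicts, and both make it too small.

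**Conclusion.** The point stands in a limited form: the minimum of 32 EMA participants is understated. Equating 29 answered prompts with 29 parenting scores conflicts with the condition under which the items are asked, and the dropout applied to the questionnaire sample is left out.

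The part that rests on the protocol's figures alone is the move from 16 to 22 per condition (32 to 44 in total) at 25% dropout. Contact gating adds to this by an unknown amount. The illustrative powers for 16 agreeing parents per condition with 25% dropout (0.68 at full contact, 0.59 at 80%, 0.47 at 60%) depend on assumptions chosen because they return 16 per condition. Under total-SD ANCOVA assumptions the loss is smaller and starts from a higher level. The error and its direction are certain; its size is not. Whether the trial's EMA test is adequately powered depends on uptake, which the document does not give.

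**What to change.** Rewrite the EMA paragraph of the Sample size section so that it:

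- states the target power and the metric of the medium effect (within-person or total SD), with the variance components used;
- sets data points per parent to 42 x 0.70 x an explicit assumed contact fraction, and shows the required n over a range of that fraction;
- inflates for the same dropout as the questionnaire sample, so that at least 22 per condition must agree to EMA before any allowance for contact.

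Add one sentence on interpretation: if EMA uptake falls below the restated minimum, research question 2 is not described as adequately powered, and its estimate is reported with a confidence interval.

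The cost is one recalculated paragraph and a less favourable stated minimum. N = 142, the assessments and the EMA schedule do not change.
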